### Design

2.1

This study will be a multicentric prospective stepped wedge controlled randomized trial (SW-CRT) with 3 clusters and 4 periods. This design was chosen because it will not be possible to do an individual randomization of patients. Indeed, there would be a high risk of contamination bias as soon as the interventional strategy will take place in the unit with the medico-pharmaceutical collaboration: it will change the habits for all patients, including control patients. The cluster cross over will be in one direction only. A sequential permutation of each cluster from control to experimental period, determined by randomization, will be made after a set time of 90 days. All the clusters will start in the control phase and end up in the interventional phase. The study design is outlined in Fig. 1.

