### Blinding

2.5

This study is single-blind. Indeed, the patient will not know if he was included in control period or interventional period. However, due to intervention type and the study design, pharmacists and physicians of the participating units will know if the patient is included in observational or experimental stage because they must do or not the intervention.

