### Sample size calculation

2.6

This study was designed according to a validated methodology of SW-CRT [23]. The Canadian meta-analysis from Taitel et al. suggests that the vaccine coverage risk ratio is 2,96 for intervention [19], but for this study, a less optimistic hypothesis was made.

Considering an intraclass correlation coefficient of 0.05, a power of 95 % and a two-sided alpha level of 5 %, a total of 684 patients must be included to highlight an absolute difference of 20 % between the control group (20 %) and the experimental group (40 %). Assuming 10 % of unusable data, the patient number were increased to 768, so 8 patients per unit and period.

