### Statistical analysis

2.8

First, descriptive statistics of the population will be done. The quantitative variables will be reported as means and standard deviation or medians and quartiles, while qualitative variables will be expressed as headcounts and proportions.

Concerning the primary outcome, the variable to explain is a complete vaccination protocol. The vaccination rate after 6 months since discharge, between control and interventional, will be analyzed by mixed logistic regression model.

We consider a potential sensitivity analysis performed by age (≥65 years vs ≤ 65 years) and comorbidities (immunocompromised patients vs non-immunocompromised) by sequentially adjusting our statistical model for the potential confounders.

For the secondary outcomes, the matching between the SNDS data and declarations of drugstores about dispensations of vaccines will be access by calculating the kappa coefficient. The other outcomes with binary variable will be parsed by mixed logistic regression model. All statistical analysis above will be stratified by type of units (medicine or surgery) and type of health facility (university hospital or hospital).

Included patients headcount will be described and summarized in a flow chart.

The statistical analysis will be performed by the Department of Biostatistics, Epidemiology, Clinical Research and Health Economics of Nîmes University Hospital by using SAS Enterprise Guide V7.1 (SAS Institute, Cary, NC, USA) or R 3.5.1 (R Development Core Team (200918). R Foundation for Statistical Computing, Vienna, Austria) or a later version.

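### Age and immunocompromised status, which the plan itself calls potential confounders, should enter one pre-specified primary model instead of an optional sensitivity analysis

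*Protocol article*

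**What the plan says.** In the protocol article, the Statistical analysis section compares complete vaccination at six months between control and intervention by mixed logistic regression. It names no patient-level covariate for that model. It then says "We consider a potential sensitivity analysis performed by age" and by immunocompromised status, to be carried out "by sequentially adjusting our statistical model for the potential confounders". The two age groups are written as 65 and over against 65 and under. The same section stratifies the analyses by type of unit and type of facility, neither of which is a patient characteristic.

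Four other sections bear on who enters each phase:

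- **Design:** a stepped wedge "with 3 clusters and 4 periods". On crossover it says: "A sequential permutation of each cluster from control to experimental period, determined by randomization, will be made after a set time of 90 days".
- **Settings/population:** each unit recruits a set number of patients per period. The number is 8 here and 16 in the Abstract, and 64 per unit over four periods agrees with 16. That inconsistency is a separate matter and does not affect this point.
- **Discussion:** the clinical pharmacist's medication reconciliation comes before any inclusion. Under Intervention, the unit's pharmacist also delivers part of the intervention.
- **Blinding:** "pharmacists and physicians of the participating units will know if the patient is included in observational or experimental stage".

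**The concern.** What is randomised is the order in which three clusters cross over. Patients enter afterwards, into a unit whose phase is already fixed and known to its staff. Unit effects remove stable differences between units, and period effects remove drift common to all units. Neither removes a change in the kind of patient a unit enrols once it moves to the intervention phase. The stratification by unit and facility type does not either.

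If older or immunocompromised patients are more or less likely to complete vaccination, and their share changes with the phase, the primary estimate mixes that change with the effect of the intervention. The authors name two such variables, yet the analysis that would deal with them is optional, and it adds covariates in turn instead of fixing one adjusted model. As written, the age variable cannot be coded for a patient aged exactly 65.

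**Working it through.** **The plan's own figure.** The required number of 684 reproduces, which shows what the design calculation contains. Inputs from Sample size calculation and Design: "Considering an intraclass correlation coefficient of 0.05", two-sided 5%, power 95%, 20% against 40%, three clusters, four periods. The Hussey-Hughes variance is

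Var = I·s²(s² + T·τ²) / [(I·U − W)s² + (U² + I·T·U − T·W − I·V)τ²].

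Here I = 3, T = 4, U = 6, W = 14 and V = 14. Total variance is 0.20 × 0.80 = 0.16, so τ² = 0.05 × 0.16 = 0.008. With 57 patients per cluster-period, s² = 0.95 × 0.16 / 57 = 0.002667.

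- Numerator: 3 × 0.002667 × (0.002667 + 0.032) = 0.0002773.
- Denominator: 4 × 0.002667 + 10 × 0.008 = 0.09067.
- Var = 0.003059, standard error 0.0553, and 0.20 / 0.0553 − 1.96 = 1.66, giving power 95.1%. With 56 patients it is 94.8%.
- N = 57 × 12 = 684.

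No patient covariate enters this calculation, so adding two to the model leaves 684 and 768 as they are.

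**Size of the bias, by arithmetic.** Let a patient group make up share π of a phase, with completion rate a in the group and b outside it, and let the intervention do nothing. The phase rate is b + π(a − b), so the spurious difference is (π_int − π_ctl) × (a − b). All inputs below are assumed, because the documents give none.

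- Shift 0.10, gap 0.10: 0.01, or 1 point.
- Shift 0.20, gap 0.20: 0.04, or 4 points.
- Example: b = 0.10, a = 0.30, share 0.50 in control and 0.70 in intervention. The rates are 0.20 and 0.24.

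Against the planned 20 points this is 1/20 = 5% to 4/20 = 20% of the effect. On the odds scale, one binary factor with odds ratio 1.5 to 3 and a shift of 10 to 30 points gives 0.7 to 5.5 points.

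**Effect on the test and on power, by simulation.** Assumed: 12 units, 4 periods, 14 patients per unit and period, two binary factors (average prevalence 50% and 30%) shifting in the same direction, fixed unit and period effects, 400 runs per row. There is no true intervention effect.

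| Shift (points) | Factor odds ratio | Without factors: log-OR, rejection | With factors: log-OR, rejection |
|---|---|---|---|
| 0 | 1.5 | −0.011, 4.2% | −0.009, 3.2% |
| 0 | 2 | −0.020, 6.0% | −0.017, 6.0% |
| 10 | 1.5 | 0.090, 5.2% | 0.007, 4.2% |
| 10 | 2 | 0.161, 7.2% | 0.009, 5.8% |
| 20 | 1.5 | 0.183, 8.8% | 0.014, 6.0% |
| 20 | 2 | 0.288, 10.2% | −0.002, 5.2% |

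The spurious odds ratios in the shifted rows run from exp(0.090) = 1.09 to exp(0.288) = 1.33. With 400 runs, the Monte Carlo standard error of a 5% rejection rate is √(0.05 × 0.95 / 400) = 1.1 points. The mildest shifted row therefore shows no clear inflation, and the strongest does.

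With no shift and a true log-OR of 0.98 (20% against 40%: ln[(0.4/0.6)/(0.2/0.8)] = 0.98), power was 84.2% without and 83.5% with the factors at odds ratio 1.5, and 81.5% and 82.0% at odds ratio 2. Adjustment neither costs nor gains power that this simulation can detect.

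**The case against.** A simpler primary model with patient covariates kept for sensitivity analysis is a recognised choice, and a condensed article may leave the covariate list to an analysis plan that is not shown. Eligibility under Settings/population is largely objective: national vaccination criteria, status confirmed by at least three sources, boosters excluded, discharge home. Reconciliation is done in both phases, and patients are said not to know their phase. All this limits the room for selection. The point remains because the article is not silent. It assigns these two variables a role, and that role is optional.

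Several stronger readings are tempting but not supported:

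- A reader might infer that staff pick among eligible patients. The article does not say so. It gives recruitment to a set number by units whose staff know the phase, and describes neither consecutive enrolment nor recruitment by someone blind to phase.
- Age and immune status might be taken as established predictors of vaccination. The article says only that they may confound.
- Adding covariates in turn might be read as data-driven selection, or as leaving the main result open. Neither follows: a primary analysis is named and the adjusted fits are labelled sensitivity analyses.
- Unit type and facility type might seem to belong in the same list. They are constant within a unit and already stratified, so they cannot correct a shift in patients within a unit.

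It is also fair that selection on willingness to be vaccinated would survive the adjustment, and that a change made after follow-up ended could itself be post hoc.

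**Conclusion.** The point holds as a modest, inexpensive improvement. The design leaves patient mix by phase unprotected, and the plan makes optional the adjustment for the two variables it names itself. Under assumed shifts and gaps of 10 to 20 points, the bias addressed is about 1 to 4 points. That would not by itself produce a 20-point difference. Nothing in the documents shows that an imbalance occurred, so it would be wrong to say that the primary estimate is biased, only that it is exposed to bias. The benefit rests on the two factors being measured and related to completion. It does not extend to unmeasured traits, and no gain in precision is claimed. The overlap at age 65 is a plain wording error, small in consequence.

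**What to change.** - Pre-specify one primary mixed logistic model that includes age (continuous, or under 65 against 65 and over) and immunocompromised status alongside the design terms.
- Report the model without these two covariates as the sensitivity analysis, as a definite commitment, in place of the sequence of adjusted fits.
- Tabulate age and immunocompromised status by phase, so that the reader can see whether the mix changed.
- Report a standardised risk difference with the odds ratio. The odds ratio becomes conditional on the covariates: with no shift and a factor odds ratio of 2, the mean log-OR in the simulation moved from 0.967 to 1.012 on adjustment.

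The cost is analysis wording. The planned sensitivity analysis already needs both variables, and the sample size is unchanged. Trial status gives the end of follow-up as 14 March 2024. If outcome data have already been analysed, the adjusted model should be labelled post hoc and shown beside the model in the article.

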### Outcomes

2.3

The primary outcome is to evaluate the rates of patients who received a complete protocol of pneumococcal vaccination six months after hospitalization. The coordinating pharmacist of the study will collect this outcome by calling the GP or the home care nurse. The national health data system (SNDS) of the NHI, which lists all medications delivered to patients [22], will also be checked to verify the dispensation of vaccines by community pharmacy. A protocol will be considered complete only if the two vaccines (PCV13 and PPSV23) were administrated.

One of the secondary outcomes will assess prescriptions of pneumococcal vaccination protocol and traceability of the indication of vaccination in the discharge letter. The clinical pharmacist will collect this information in the unit at discharge. Later on, the rates of incomplete vaccination protocol 6 months after the hospitalization will be evaluated. The rate of incomplete protocols will be calculated by dividing the number of patients with incomplete vaccination protocols to the total number of patients, transformed in percents. An incomplete protocol is determined by dispensation and administration of PCV13, not followed by administration of a second injection of PPSV23. As for the primary outcome, the SNDS will be checked and the healthcare staff administrating will be contacted to confirm the administration of the first vaccine but not the second one. The SNDS will also be consulted to analyze the primary dispensation of vaccines by community pharmacy 6 months after hospitalization. The matching between the SNDS data and declarations of community pharmacies about dispensations of vaccines will be also evaluated. The declarations of community pharmacies will be collected after a call by the pharmacist coordinating this study. Finally, a subgroup analysis will be done to compare the difference between clinical and surgical units and university hospitals and hospitals.

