## Discussion

3

This trial will assess the impact of the collaboration between pharmacist and physician on increasing the pneumococcal vaccination of at-risk patients when they return home after hospitalization.

The IP-VAC trial [24], a single center study made by the Nimes University Hospital preliminary to OPTIVACC, showed an increase of vaccines dispensation by community pharmacy. By collecting data on vaccine administration from GPs or home nurses, OPTIVACC study wants to demonstrate an impact on pneumococcal vaccination coverage. To harmonize the data collection, phone calls will be centralized and performed by one officer. In addition, consultation of the NHI database at the end of the study should allow an exhaustive collection of all the vaccine doses administered to the patients.

In addition, consultation of the NHI database at the end of the study should allow an exhaustive collection of vaccines administered to the patients. Intervention will be evaluated in two types of care units (clinical and surgical) and two types of establishments (hospitals and university hospitals). The aim of these comparisons is to define in which context the intervention will be most relevant, in order to target eligible care units.

Patient recruitment will be a critical point of this study, even though there are many indications for pneumococcal vaccination. Firstly, it is difficult to check patients' vaccination status. According to a study carried out as part of the “INNO'vaccins programme”, one patient in two does not know whether he/she is up to date with his/her vaccinations [25]. For this reason, medication reconciliation, a process carried out by the clinical pharmacist to list all patient's medication on hospital admission, is the first step before including a patient in the study.

Although all of the participating centers carry out clinical pharmacy activities, most of them have never conducted clinical research projects. In this sense, initial training of the centers' personal and coordination of the project are two key points for the success of the study, particularly in terms of patients’ recruitment and follow-up.

Patient follow-up will run for a period of six months after discharge to allow the patient to complete the vaccination protocol, which takes at least 8 weeks.

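### Stratifying every analysis by unit type and facility type does not test the between-setting comparison that the protocol sets out to make; a phase-by-subgroup interaction should be named.

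*Protocol article*

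**What the plan says.** Three places in the protocol article bear on this.

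- **Aim (Outcomes, 2.3).** Among the secondary outcomes, "a subgroup analysis will be done to compare the difference between clinical and surgical units and university hospitals and hospitals". The Background likewise says that potential differences between types of unit and facility are to be assessed.
- **Intended use (Discussion, 3).** "The aim of these comparisons is to define in which context the intervention will be most relevant, in order to target eligible care units".
- **Method (Statistical analysis, 2.8).** "All statistical analysis above will be stratified by type of units (medicine or surgery) and type of health facility (university hospital or hospital"). The section names no interaction term or other contrast between strata. The sentence follows the description of the primary model as well as the secondary ones, so taken literally it covers the primary analysis too.

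**The concern.** The aim is a comparison of two effects, and the stated method gives two effects side by side. Whether they differ is a separate question with its own standard error. A significant result in one stratum and a non-significant result in the other does not answer it.

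This matters because the subgroup results have a stated practical use, the choice of care units. By Table 1 each factor splits the 12 units 6 and 6, so each stratum holds half the planned patients. A trial sized for the whole sample then has only moderate power in each half, and with moderate power two strata that share the same true effect will often fall on opposite sides of 5%. Settings could be ranked on that alone.

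**Working it through.** **Inputs.** From Sample size calculation (2.6): "a total of 684 patients must be included", "intraclass correlation coefficient of 0.05", stated power 95%, "a two-sided alpha level of 5"%, and "an absolute difference of 20 % between the control group (20 %) and the experimental group (40"%). The 684 is raised to 768 for 10% unusable data. From Design (2.1): 3 clusters, 4 periods. From Trial status: 646 patients included; less the planned 10% this is 581. The outcome variance is not stated, so I take 0.16 (control rate, 0.2 × 0.8), 0.20 (average of 0.16 and 0.24) and 0.21 (pooled, 0.3 × 0.7).

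The Abstract gives 16 patients per unit and period; sections 2.2 and 2.6 give 8. 12 × 4 × 16 = 768, whereas 12 × 4 × 8 = 384. These passages need reconciling. The figures below use the stated totals.

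**Step 1: reproduce 684.** The Hussey-Hughes variance of the effect is

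Is(s + Tτ²) / [(IU − W)s + (U² + ITU − TW − IV)τ²],

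where I is the number of clusters, T the number of periods, s the within-cluster variance divided by patients per cluster-period, and U, W and V the usual sums over the exposure pattern. With I = 3, T = 4, U = 6, W = V = 14, variance 0.16 (τ² = 0.008, within-cluster 0.152) and 57 patients per cluster-period (3 × 4 × 57 = 684):

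- s = 0.152/57 = 0.002667
- variance = 0.0002773/0.09067 = 0.003059, SE 0.0553
- power = Φ(0.20/0.0553 − 1.96) = 95.1%

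So 684 is reproduced with the control-rate variance and 3 clusters. With variance 0.20 or 0.21 the same formula gives 90% or 88% power at 684. The subgroup figures are therefore shown under more than one variance.

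**Step 2: power in one half, scaled from the stated 95%.** The standardised effect is 1.960 + 1.645 = 3.605. In half the sample it is 3.605/√2 = 2.549. Power = Φ(2.549 − 1.960) = 72.2%.

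**Step 3: chance that exactly one stratum is significant, same 20-point effect in both.** This is 2p(1 − p), treating the strata as independent: 2 × 0.722 × 0.278 = 40.1% per factor.

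**Step 4: range.** Hussey-Hughes values cover analysis by 3 clusters or by 6 units per half.

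| Usable patients | Scaled from 95% | Variance 0.16 | Variance 0.20–0.21 |
|---|---|---|---|
| 768 | 35% | 31–34% | 41–44% |
| 684 | 40% | 36–38% | 44–47% |
| 646 | 42% | 38–41% | 46–48% |
| 581 | 45% | 42–44% | 48–49% |

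Values below 35% arise only if all 768 patients are usable, with none of the planned loss, and the smallest variance applies.

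**Step 5: dependence on the true common effect (scaled, 684).**

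| True effect, points | 0 | 5 | 10 | 15 | 20 | 25 | 30 |
|---|---|---|---|---|---|---|---|
| Exactly one significant | 9.5% | 18% | 37% | 50% | 40% | 20% | 6% |

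**Step 6: the interaction test.** When the effects are equal, a two-sided 5% interaction test declares a difference 5% of the time per factor. Its SE is √2 × √2 = 2 times the main-effect SE. Scaled from 95% power, the chance of detecting a 20-point difference between effects is Φ(3.605/2 − 1.960) = Φ(−0.158) = 44%. For a 10-point difference it is Φ(0.901 − 1.960) = about 14%. At variance 0.20 with 6 units and 342 patients per half, the stratum SE is 0.083, so the interaction SE is √2 × 0.083 = 0.118, about 12 points on the risk-difference scale.

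**The case against.** The strongest reply is that the protocol nowhere says a difference will be declared because one stratum is significant and the other is not. Section 2.3 promises a comparison, section 2.8 is a condensed sentence, and an interaction test could sit in the unseen analysis plan. This stands in part. A reader might infer that a false difference would be declared nearly half the time. The documents do not support that: they give no such decision rule, they do not exclude an interaction test, and the rate depends on the true effect, the variance and the usable number. What remains is that the article does state a method, and that method does not answer the question it poses.

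A reader might also infer that the two factors are crossed, leaving 3 units per cell. The Abstract and section 2.3 read as two separate one-way splits of 6 units against 6, so no argument can be built on crossed cells.

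The Discussion sentence on targeting states an aim and does not commit to a recommendation, and the subgroup analysis is secondary. Both limit the seriousness of the point.

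Finally, an interaction in a logistic model is on the odds-ratio scale, whereas the 12-point SE is on the risk-difference scale. The scale for judging a difference must be named.

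**Conclusion.** The point holds in a limited form. The stated aim is a comparison of effects between settings, and the stated analysis, stratification alone, does not test it. If significance were compared across strata, equal 20-point effects would look discordant about 40% of the time per factor, roughly 35 to 49% over plausible variances and usable numbers.

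That figure assumes a true effect near the design value, equal halves and independent strata. The last is approximate, because the clinical and surgical units of a university hospital share a site. With no effect anywhere the figure is 9.5%; at 30 points it is 6%. It measures what the wording leaves open and is not an error rate that the protocol has adopted. The point concerns a secondary aim with a practical use and does not undermine the validity of the primary comparison.

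**What to change.** Replace the stratification sentence in section 2.8 so that it says the following:

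1. The primary result is a single mixed logistic model on all patients, not split by setting.
2. For each factor separately, a model on all patients adds the interaction: phase by unit type in one, phase by facility type in the other.
3. A difference between settings is judged only on the interaction and its 95% CI, on the odds-ratio scale of the stated model.
4. Stratum estimates are taken from that same model and reported as descriptive.
5. These analyses are labelled exploratory.

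The cost is analysis and reporting wording only; no further patients or data are needed, and the change remains possible although follow-up has ended. The downside should be stated alongside: the interaction is imprecise (SE about 12 points on the risk-difference scale at variance 0.20, and about 44% power for a 20-point difference in effects). A non-significant interaction will therefore not show that settings are alike, and any choice of units to target should carry that caution.
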